## Abstract

**Background:**

Multiple sclerosis (MS) is a chronic disease affecting multiple functional aspects of patients’ lives. Depression and anxiety are common amongst persons with MS (PwMS). There has been an interest in utilizing patient-reported outcome measures (PROMs) to capture and systematically assess patient’s perceptions of their MS experience in addition to other clinical measures, but PROMs are not usually collected in routine clinical practice. Therefore, this study aims to systematically incorporate periodic electronically administered PROMs into the care of PwMS to evaluate its effects on depression and anxiety.

**Methods:**

A randomized controlled trial will be conducted with patients allocated 1:1 to either intervention or conservative treatment groups. Patients in the intervention group will complete PROMs at the start of the study and then every 6 months for 1 year, in addition to having their MS healthcare provider prompted to view their scores. The conservative treatment group will complete PROMs at the start of the study and again after 12 months, and their neurologist will not be able to view their scores. For both groups, pre-determined critical PROM scores will trigger an alert to the patient’s MS provider. The difference in change in Hospital Anxiety and Depression Scale score between the intervention and conservative treatment groups at 12 months will be the primary outcome, along with difference in Consultation Satisfaction Questionnaire and CollaboRATE scores at 12 months, and proportion and type of healthcare provider intervention/alerts initiated by different PROMs as secondary outcomes.

**Discussion:**

This study will determine the feasibility of utilizing PROMs on an interval basis and its effects on the psychological well-being of PwMS. Findings of this study will provide evidence on use of PROMs in future MS clinical practice.

**Trial registration:**

This trial is registered at the National Institutes of Health United States National Library of Medicine, ClinicalTrials.gov NCT04979546. Registered on July 28, 2021.

**Supplementary Information:**

The online version contains supplementary material available at 10.1186/s12883-023-03090-0.

## Background

Multiple sclerosis (MS) is a disease that can affect physical, cognitive, psychological, and social functioning [1–3]. While physical symptoms and disability are typically the focus of routine care, there is an increasing recognition of psychiatric comorbidity in multiple sclerosis, particularly depression and anxiety; the presence of depression and anxiety are known to reduce quality of life in persons with MS (PwMS) [4–6]. A large meta-analysis including over 87,000 PwMS estimates prevalence of depression and anxiety at 30.5% and 22.1%, respectively [7], emphasizing the heightened burden of mental illness in this population. The downstream effects of depression and anxiety in MS are multifaceted beyond the negative impact upon quality of life, having been linked to nonadherence to disease modifying treatments [8], increased rate of hospitalizations [9], and increased mortality [10].

Patient-reported outcome measures (PROMs) give patients the opportunity to describe their symptoms and the impact of care in a consistent and systematic fashion [11], and the incorporation of PROMs into several large registries in North America and Europe highlights their increasing relevance in MS research [12–15]. PROMs are thought to be important in optimizing the management of PwMS in providing the patient’s perspective of their disease [16]. Additionally, use of PROMs between clinic visits could provide real-time information for healthcare providers, which is vital in a disease with episodic disability and fluctuating symptoms over time. Even though such information could help clinicians provide patient-centred care and patients track their progress, it is not usually collected on a routine basis due to time limitations and system issues within clinics, amongst other factors [17].

Electronic data capture could help overcome these difficulties, as patients will have the flexibility to provide the information from anywhere and the data will automatically be saved in an electronic database that can be accessed anytime by patients and their healthcare providers. This will allow patients to be fully informed about their condition, be more engaged in their care, track their progress, and receive any notifications or alerts regarding their care. It will also allow healthcare providers to systematically track the patient’s progress, better prepare for clinic visits and to better provide care based on patient’s individual needs. This patient-centred approach could enhance the care that PwMS receive. Regular use of PROMs also has potential for PwMS to provide information about their symptoms and quality of life (QoL) before their visits. This could free up time during clinic visits to address identified concerns and needs, and then come up with a management and support plan based on those needs.

In addition to offering data to providers, routine PROMs may potentially reinforce patient activation and engagement, which are related terms to describe a patient having adequate knowledge and ability to actively participate and manage their healthcare, and the interventions and behaviours demonstrating the former, respectively [18]. Patient activation is associated with improved health outcomes, enhanced healthcare experiences, and lower costs across different chronic diseases [18]. PROMs support patient activation and engagement by providing a platform for patients to voice the impact of their disease through the lens of their unique experiences and lifestyle [19]. Thus, there is considerable motivation to incorporate PROMs into routine clinical care, but among issues including logistical and technological challenges, the optimal timing and frequency of reporting PROMs is unknown [19–22].

Furthermore, using PROMs longitudinally is not known to affect mental health outcomes in PwMS by providing healthcare providers objective measures to track scores and intervene when needed. The present study seeks to fill this knowledge gap by examining the systematic incorporation of electronically administered PROMs into the care of PwMS and exploring their effects on depression and anxiety.

## Objectives

The aim of this study is to evaluate the systematic use of PROMS in PwMS in both an academic MS clinic and in community neurology office practices. Specifically, the goal is to examine the impact of regular utilization of PROMs on patients’ mental health outcomes and satisfaction with care, and the difference in those measures depending on PROM administration frequency. We hypothesize that:Patients completing PROMs more frequently will have a greater improvement in depression and anxiety scores in PwMS.Providers will initiate an intervention for a higher proportion of PwMS completing PROMs more frequently compared to usual care.PwMS completing more frequent PROMs will have a greater satisfaction in care provided by their clinicians.

## Methods

This protocol is in accordance with Standard Protocol Items: Recommendations for Interventional Trials (SPIRIT) 2013 guidelines. Ethics approval was obtained by the University of Alberta Research Ethics Office (Health Research Ethics Board – Health Panel ID: Pro00111593).

### Study population

Participants will be PwMS managed by a neurologist or MS nurse practitioner in northern Alberta, Canada. This includes a tertiary care academic centre (the Kaye Edmonton Clinic – Northern Alberta MS Clinic affiliated with the University of Alberta in Edmonton, Alberta, Canada), a community hospital-based outpatient MS clinic (MS Clinic, Red Deer Regional Hospital in Red Deer, Alberta, Canada) and additional private community neurologist practices (Westmount Neurology Clinic, and Edmonton Specialists Clinic, both in Edmonton, Alberta, Canada).

Inclusion criteria are:A confirmed diagnosis of MS by a qualified healthcare provider. All subtypes falling under the diagnosis of multiple sclerosis including relapsing–remitting, secondary progressive, and primary progressive, among others, are eligible to participate.Active patient of an Alberta-based neurologist/MS nurse practitioner.Able/willing to complete informed consent and electronic PROM questionnaires.Able to use a computer/smartphone.English-speaking.

Exclusion criteria are:A suspected but not confirmed diagnosis of MS, a diagnosis of clinically/radiologically isolated syndrome, or a central nervous system inflammatory disorder other than MS.PwMS not being managed by a participating neurologist/MS nurse practitioner.Unwilling/unable to provide consent.Unwilling/unable complete the electronic PROM questionnaires.Cannot speak English.Under the age of 18.

### Participant recruitment

Patients will be contacted and informed about the study via four primary methods:Participating outpatient community neurologists/MS nurse practitioners will provide rosters of PwMS, and patients will be contacted via secured and encrypted email messaging.All patients (*n* = 246) who previously participated in a related study by our group [23] will be contacted via email/phone number; as part of the aforementioned study, they have already consented to be contacted to participate in future research projects.Patients with MS providers at the Northern Alberta MS Clinic will be contacted via secured messaging through MyChart® (Epic Systems Corporation©).Advertisement posters (Supplementary Fig. 1) will be displayed in participating clinics. Patients will be able to access a link via Uniform Resource Locator (URL) or Quick Response (QR) code to provide informed consent and self-registration.

Health care providers (MS neurologists and nurse practitioners) will be identified by the researchers and contacted directly via email, telephone, or in-person conversation. Groups of providers (those based out of the Kaye Edmonton Clinic at the University of Alberta and community neurologists with private practices) will be given formal presentations on the research protocol and aims, and the extent of the providers’ participation.

### Patient enrolment

Interested patients responding to our recruitment methods will be given a link to the Research Electronic Data Capture (REDCap) tools and services at the University of Alberta, where they will be provided with further study information and asked to provide digital informed consent for self-registration (Supplementary Fig. 2). During self-registration, they will select their MS provider from a drop-down list. Our research team will then assign them to a Data Access Group (DAG) to enlist the patient in a roster based on their provider; this will allow each provider to confidentially view their own patients’ PROM scores throughout the study.

### Design

This study is a randomized controlled trial with the patient as the unit of randomization. Patients will be randomized electronically in a 1:1 ratio to the intervention or conservative groups at study enrolment using a native REDCap randomization module to ensure allocation concealment. The timeline of the study protocol is depicted in Fig. 1.

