**Fig. 1 Fig1:**
[figure not shown]
Study protocol timeline and flow chart. MS, multiple sclerosis; PROMs, patient reported outcome measures; CSQ; consultant satisfaction questionnaire

Participants are randomly assigned in a 1:1 ratio to one of two groups:*Intervention group*: All participants randomized to the intervention group will be asked to complete the following validated questionnaires at baseline and approximately every 6 months for a total of 12 months:Hospital Anxiety and Depression Scale (HADS) score [24]Quality of life as measured by EuroQol five-dimensional questionnaire (EQ5D) [25]Fatigue as measured by Modified Fatigue Impact Scale (MFIS) [26]The Patient Determined Disease Steps (PDDS) [27]Patient Health Questionnaire-9 (PHQ-9) [28]Open ended text response to (limit 280 characters) “What are the top 3 things you would like your MS healthcare provider to know about you right now?” – to be referred as the 3-item prompt (3IP). Completed questionnaires will be sent to the treating provider via a secured link using encrypted email to review the corresponding scores and the text response to the 3IP.*Conservative group*: All participants randomized to the conservative group will be asked to complete the same questionnaires as above, however only at baseline and at the end of the study at 12 months. Additionally, the treating provider will only be prompted to review the text response to the 3IP and will not be able to access the PROM questionnaire scores.

For both groups, providers will be able to document via REDCap whether they have reviewed the aforementioned items and their response/intervention, if applicable (Supplementary Fig. 3). Examples of provider responses would be phone calls to patients, scheduling earlier appointments, alterations to medication regimens, referral to another health or medical provider, and/or messaging the patient via secure email messaging system; a free text response will also be included to allow documentation of alternative interventions if required. Due to initial lack of provider engagement, providers will be incentivized with token of appreciation ($10 Amazon gift card) for each instance of documenting they have reviewed (and if applicable, enacted healthcare provider intervention in response to) their patients’ PROM scores and/or text responses to 3IP. There will be no difference in incentive if providers offer an intervention (eg. telephone call, referral to another healthcare provider or service, etc.).

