### Data collection

The questionnaires will be delivered electronically to the patient at baseline for both conservative and intervention groups. For patients in the intervention group, questionnaires will be delivered electronically again at 6 months and at the end of the study at 12 months; in the conservative group, questionnaires will be delivered electronically again at the end of the study at 12 months. Initial CSQ and CollaboRATE surveys will be sent to both groups at baseline and at the end of the study. Patients will be sent an email to ask them to complete the questionnaires, with 2 follow-up reminders (1 week and 2 weeks) after the initial electronic contact. For provider exit surveys, mean and median values will be calculated from questions assessed on a Likert scale. Proportion of responses on each multiple choice answers will be determined on the one multiple choice question. Open ended responses will be assessed qualitatively.

Study methods, data management, and biostatical support is supplied by EPICORE Centre, Department of Medicine/Pharmacology, Faculty of Medicine and Dentistry (www.epicore.ualberta.ca). Data for the study will be collected and managed using REDCap at the University of Alberta. REDCap is a secure, web-based software platform designed to support data capture for research studies, providing 1) an intuitive interface for validated data capture; 2) audit trails for tracking data manipulation and export procedures; 3) automated export procedures for seamless data downloads to common statistical packages; and 4) procedures for data integration and interoperability with external sources [31, 32]. Data from administered PROMs through REDCap will allow for centralized data collection capable of export for future analysis.

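### Baseline HADS appears to be collected after randomisation, and no completed baseline is required for allocation, so randomised patients who never return it drop out of the primary change-score test

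*Protocol article*

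**What the plan says.** All references are to the protocol article.

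- **Patient enrolment** describes digital consent and self-registration, in which "During self-registration, they will select their MS provider from a drop-down list". The research team then places the patient on that provider's roster. No questionnaire is mentioned at this step.
- **Design** states: "Patients will be randomized electronically in a 1:1 ratio to the intervention or conservative groups at study enrolment". It leaves the sequence of events to a figure: "The timeline of the study protocol is depicted in Fig. 1".
- **The group descriptions under Fig. 1** put the baseline request to people who already have an arm. For one arm: "All participants randomized to the intervention group will be asked to complete the following validated questionnaires at baseline". For the other: "All participants randomized to the conservative group will be asked to complete the same questionnaires as above, however only at baseline".
- **Data collection** adds: "The questionnaires will be delivered electronically to the patient at baseline for both conservative and intervention groups". It also says: "Patients will be sent an email to ask them to complete the questionnaires, with 2 follow-up reminders (1 week and 2 weeks".
- **Study population** lists as an exclusion: "Unwilling/unable complete the electronic PROM questionnaires".
- **Data analysis** tests the change in HADS-D and HADS-A from baseline to 12 months with an independent t-test. Last observation carried forward applies once cumulative missingness exceeds 10%. Only data assessors are described as blinded.
- **Sample size** gives 356, inflated by 10% to 392 for dropouts, losses to follow-up and withdrawals of consent.

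**The concern.** A change score needs two values. If the first is requested only after allocation, by email and with a response window of about two weeks, some randomised patients may never supply it. They then leave the primary comparison after randomisation, so the analysed set is no longer simply the randomised set. Precision falls, and balance between the arms is no longer guaranteed by design.

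A second, weaker worry concerns the baseline value itself. Intervention patients' scores are sent to their provider, while conservative patients' scores are withheld apart from critical-score alerts. A patient who knew the arm before answering might report differently, and the primary test subtracts that answer.

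**Working it through.** **Step 1. The order of events.**

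| Section | Event | Baseline questionnaire mentioned? |
|---|---|---|
| Patient enrolment | Consent, self-registration, choice of provider, roster | No |
| Design | Randomisation at enrolment | No |
| Group descriptions under Fig. 1 | Participants randomised to each arm are asked for questionnaires | Yes, after the arm is named |
| Data collection | Electronic delivery at baseline to both groups; email and two reminders | Yes, by group |

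The natural reading is enrolment, randomisation, then baseline request. No section contradicts it, but none states it outright. The exclusion criterion screens for willingness or ability, not for a submitted form.

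**Step 2. What the analysis does with a missing baseline.** Change = 12-month HADS minus baseline HADS. Without a baseline the change is undefined. Last observation carried forward copies an earlier value to a later time, so it cannot fill the first one. The linear mixed model in Data analysis is described for multivariable adjustment, not as the primary test.

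**Step 3. Reproduce the plan's sample size.** Inputs from Sample size: difference 0.298, two-sided alpha 0.05, power 80%, independent t-test. I read 0.298 as standardised (SD 1); this is an assumption.

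- Normal approximation: n per arm = 2 × (1.96 + 0.842)² / 0.298² ≈ 176.8, so 177 per arm and 354 in total.
- t-test solution: 177.7, so 178 per arm and 356 in total, as stated. Power at 178 per arm is 0.801.
- Inflation: 356 × 1.1 = 391.6, so 392 (196 per arm), as stated.

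**Step 4. Illustrate the loss.** The documents give no rate of baseline non-response, so b below is an assumption. Losses are taken as equal in the two arms. Power is for the two-sided t-test at 0.298 SD.

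(a) Missing baseline on top of the full 10% later loss: analysable N = 392 × (1 − b) × 0.9.

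| b | Analysable N | Power |
|---|---|---|
| 0% | 353 | 0.797 |
| 5% | 335 | 0.776 |
| 10% | 318 | 0.754 |
| 15% | 300 | 0.730 |

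(b) Missing baseline counted inside the 10% allowance: if the total loss is 10%, 392 × 0.9 = 353 remain and power is 0.797, close to the planned 80%.

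**Step 5. Knowledge of the arm at baseline.** This needs two facts: that baseline follows allocation (inferred in step 1) and that patients know their arm when they answer. The article does not say when patients learn their arm. No size can be calculated.

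**The case against.** The strongest reply is that the order is not stated and that the figure which would show it is not available here. The group descriptions set out each arm's whole schedule, as protocols often do, and the reminder sentence covers questionnaires in general. Enrolment and baseline could be one online session, or baseline could come first. This stands, and it is why the point is worded as what appears to happen.

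A reader might infer that the baseline is in fact contaminated by knowledge of the arm and that the primary contrast is biased by a definable amount. The documents do not support this. They are silent on when the arm is revealed. Both arms receive the same questionnaires at baseline, and in both arms critical scores alert the provider and the free-text answer reaches the provider. Routine scores are sent only after completion, so provider review cannot influence the first HADS. A reporting tendency that persisted to 12 months would also cancel, partly or wholly, in a change score.

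A reader might also take the power loss as established. It is not: the rates are assumed, a patient who never returns baseline could reasonably be counted as a dropout within the 10%, and requiring patients to be able and willing to complete the questionnaires makes high early non-response less likely.

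Finally, the handling of incomplete records is often left to an analysis plan that is not shown. That is fair for detail. But the article itself fixes the primary test and the carry-forward rule, and neither can use a patient without a baseline. The order of randomisation and baseline is design, on which the article does speak.

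**Conclusion.** The point holds in a limited form. As written, randomisation takes place at enrolment, the baseline request appears to follow it, and nothing requires a completed baseline before allocation. Randomised patients without a baseline HADS therefore cannot enter the primary t-test, and the stated missing-data rule does not recover them. This consequence does not depend on whether patients know their arm.

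The cost in power ranges from almost nothing (missing baselines absorbed by the 10% allowance) to about 2 to 7 percentage points (5% to 15% missing on top of it). These figures rest on assumed rates, equal loss in both arms, and 0.298 read as a standardised difference. Bias from answering with knowledge of the arm is a possibility only, with no size attached.

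The change is worth making because it is cheap and still useful: Trial status reports 191 enrolled at manuscript submission, so 392 − 191 = 201 planned patients had yet to be enrolled.

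**What to change.** 1. **Remaining enrolment.** Set REDCap to randomise only once the baseline set is submitted: consent, eligibility, baseline questionnaires, then allocation. If this is already how the trial runs, one sentence in Design saying so settles the question of order.
2. **Patients already randomised.** Use REDCap time stamps to report, by arm, how many baselines post-date allocation and how many are missing.
3. **Primary analysis.** Replace the t-test on change with a likelihood-based repeated-measures model for HADS-A and HADS-D in which baseline is one of the outcomes, with a mean common to both arms. Patients with only a 12-month HADS then contribute. Randomisation justifies the common mean when baseline precedes allocation. For baselines that post-date it, the common mean is an assumption, so add a sensitivity comparison of 12-month HADS alone if step 2 shows many of these.

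The cost is a change in survey order, a count from existing time stamps, and a short change to the analysis text. The downside is that a few consenting patients who never complete baseline will not be randomised.
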